# Safety and efficacy of C1-inhibitor in traumatic brain injury (CIAO@TBI): study protocol for a randomized, placebo-controlled, multi-center trial

**DOI:** 10.1186/s13063-021-05833-1

**Published:** 2021-12-04

**Keywords:** Traumatic brain injury, C1-inhibitor, Neuroinflammation, Randomized controlled trials

## Abstract

**Background:**

Traumatic brain injury (TBI) is a major cause of death and disability across all ages. After the primary impact, the pathophysiologic process of secondary brain injury consists of a neuroinflammation response that critically leads to irreversible brain damage in the first days after the trauma. A key catalyst in this inflammatory process is the complement system. Inhibiting the complement system could therefore be a therapeutic target in TBI.

**Objective:**

To study the safety and efficacy of C1-inhibitor (C1-INH) compared to placebo in patients with TBI. By temporarily blocking the complement system, we hypothesize a decrease in the posttraumatic neuroinflammatory response resulting in a less unfavorable clinical outcome for TBI patients.

**Methods:**

CIAO@TBI is a multicenter, randomized, blinded, phase II placebo-controlled trial. Adult TBI patients with GCS < 13 requiring intracranial pressure (ICP) monitoring will be randomized, using block randomization, within 12 h after trauma to one dose 6000 IU C1-INH or placebo. A total of 106 patients will be included, and follow-up will occur up to 12 months. The primary endpoints are (1) Therapy Intensity Level (TIL) Scale, (2) Glasgow Outcome Scale-Extended (GOSE) at 6 months, and (3) complication rate during hospitalization. Outcomes will be determined by a trial nurse blinded for the treatment allocation. Analyses will be conducted in an intention-to-treat analysis.

**Discussion:**

We expect that C1-INH administration will be safe and potentially effective to improve clinical outcomes by reducing neuroinflammation in TBI patients.

**Trial registration:**

ClinicalTrials.gov NCT04489160. Registered on 27 July 2020. EudraCT 2020-000140-58

**Supplementary Information:**

The online version contains supplementary material available at 10.1186/s13063-021-05833-1.

## Background

Traumatic brain injury (TBI) is a major cause of death and disability around the world. In Europe, over one million traumatic brain injury (TBI) patients are admitted to the hospital yearly, of whom 75,000 people die [1, 2]. This debilitating morbidity leads to enormous societal costs [3]. Therapies and guidelines that have been demonstrated to improve the outcomes after TBI are still limited, especially in the management of severe TBI (s-TBI), defined by Glasgow Coma Scale (GCS) 3–8 [4]. Patients with s-TBI have a high mortality rate, estimated at 30–40% in observational studies [1]. Survivors of s-TBI experience a substantial burden of physical, psychiatric, emotional, and cognitive disabilities that disrupt their lives, their proxy family members, and their social surroundings. Adequate treatment strategies are therefore pivotal. TBI comprises a dynamic pathophysiology that evolves over time, consisting of primary injury after the traumatic hit, followed by systemic disorders which lead to secondary injury [5]. The overshooting inflammatory response and delayed formation of brain edema, mostly seen around the third day after trauma, are characteristics of secondary brain injury, which are in turn related to a complicated clinical course, delayed recovery, late morbidity, and mortality in TBI [6–8].

The complement system forms the first line of defense against microorganisms and is critical in sensing tissue damage. Complement activation can be mediated by three distinct pathways: the classical pathway, the lectin pathway, and the alternative pathway [9]. Multiple experimental studies have identified a pathophysiologic role of the complement system in contributing to posttraumatic neuro-inflammation, disruption of the blood-brain barrier, secondary neuronal damage, and neuronal cell death after TBI [10–14]. Activation of the complement system in s-TBI results in a cascade of events including increased vascular permeability and activation of microglia and astrocytes, ultimately resulting in inflammatory reactions in and around contusion areas [15, 16]. In addition, it triggers a sustained degenerative mechanism of reduced dendritic and synaptic density and inhibited neuroblast migration several weeks after TBI in animal models [17]. In severe TBI patients, elevated complement factors have been found in the serum [18, 19] and in the ventricular cerebrospinal fluid (CSF) directly after initial trauma [20, 21].

Complement inhibition is therefore considered to be a potentially important target of TBI treatment. Inhibitors of C3 or C5 convertases, membrane attack complex (MAC) formation, and C1-inhibitor (C1-INH) have been identified to prevent secondary neurologic damage and improve neurologic performance in mice by reducing microglia activation, apoptosis, and axonal loss [22–26]. C1-INH is an inhibitor of the classical, lectin, and alternative pathway, which additionally interact with the contact and coagulation system, and is currently indicated for the treatment of hereditary angioedema (HAE) [27–29] (Fig. 1). Because of its favorable safety profile, it has been used to treat other inflammatory diseases, such as sepsis or ischemic reperfusion injury [30, 31].

**Fig. 1 Fig1:**
[figure not shown]
Contact, complement, coagulation, and fibrinolytic systems and targets of C1-INH. *Abbreviations*: MAC, membrane attack complex; HMWK, high-molecular-weight kininogen; C1-INH, C1-inhibitor; t-PA, tissue plasminogen activator; MASPs, mannose-associated serine protease. *Explanation*: C1-INH is directed at all three pathways of the complement system, but has also an effect on the contact, fibrinolytic, and coagulation system

High-quality preclinical evidence suggests a significant role of the complement system in the pathophysiology of neuroinflammation. As complement inhibition is potentially an important aspect of TBI treatment to attenuate neuroinflammation, the CIAO@TBI multicenter, randomized, blinded, placebo-controlled trial aims to assess the safety and efficacy of C1-INH in TBI patients. It is hypothesized that C1-INH can be beneficial in the treatment of s-TBI by decreasing the detrimental neuroinflammation and preventing secondary brain injury to ensure a more favorable functional outcome and a less hampered quality of life for the future TBI patients.

## Methods

### Trial design

Complement inhibition: Attacking Overshooting inflammation @fter Traumatic Brain Injury (CIAO@TBI) is a multicenter, randomized, blinded, placebo-controlled, phase II trial in patients with TBI. The protocol is designed in accordance with the Standard Protocol Items: Recommendation for Interventional Trials (SPIRIT) 2013 Checklist (Additional file 1) [32]. Patients will be recruited in three-level one trauma centers, including the coordinating neurotrauma research unit of University Neurosurgical Center Holland seated at Leiden University Medical Center (LUMC) and Haaglanden Medical Center (HMC) in close collaboration with Erasmus Medical Center Rotterdam (EMC) and Amsterdam University Medical Centers, location AMC. Patients will be randomized at the ICU in the first 12 h after trauma to receive (1) one dose of C1-INH 6000 IU intravenously (IV) or (2) one placebo injection with 0.9% saline IV.

### Objectives

The main objective of the CIAO@TBI trial is to determine the safety and efficacy of C1-INH in patients with s-TBI. The primary endpoints are (1) efficacy: intracranial pressure (ICP) directed Therapy Intensity Level (TIL), GOSE at 6 months after discharge, and (2) safety: complication rate during hospitalization.

### Trial population and eligibility

All TBI patients presenting to participating hospitals are potentially eligible for this trial. The inclusion criteria are (1) age > 18 years, (2) clinical diagnosis of TBI with GCS < 13 on admission (with visible intracranial pathology on CT), and (3) invasive intracranial pressure monitoring by intra-parenchymatous transducer or ventricular catheter placement and management of increased ICP for at least 24 h. The exclusion criteria are (1) a clear, non-traumatic cause of low GCS on admission (e.g., toxic or cardiac cause); (2) not expected to survive more than 24 h after admission with the decision to abstain from aggressive treatment and induce palliative care; (3) brain death on arrival in the participating centers; (4) severe pre-trauma disability, defined as being dependent on other people; (5) known prior history of sensitivity to blood products or C1-INH; (6) patients with a history of hereditary angioedema (if known at admission); (7) patients with a history of thrombosis (deep vein thrombosis, cerebral venous sinus thrombosis, or pulmonary embolism) (if known at admission); and (8) patients that are pregnant (if known at admission).

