### Trial interventions

The intervention is the IV administration of C1-INH compared to a placebo (0.9% saline). A single dose of 6000 IU will be administered within 12 h after trauma. Blood samples (2 EDTA, 1 serum, and 1 citrate tube) will be drawn from both patient groups before administration and at 6, 12, 24, 48, 72, and 96 h after administration of C1-INH or placebo in the ICU. Moreover, if an external venticular drain (EVD) is placed as part of standard care to reduce CSF pressure, additional liquor samples will be drawn before administration and 24, 48, 72, and 96 h after administration of C1-INH or placebo in the ICU. All samples will be centrifuged and aliquoted in 500 μl samples as quickly as possible and afterwards stored at − 80 °C. Other interventions are unaltered from local treatment protocols and will include standard of care in both groups. This might include concomitant therapies, such as a decompressive craniectomy. During hospitalization, patients are closely monitored for (serious) adverse events (SAEs). Moreover, health-related questionnaires will be filled out by the patients or proxies at discharge and at 3 months, 6 months, and 12 months after head trauma. A flowchart of the study design is shown in Fig. 2. All study procedures will be performed according to the designated study operating procedures (SOPs).

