### Primary endpoints

#### Efficacy: Therapy Intensity Level (TIL) Scale

To measure the direct effect on the mechanism of action of C1-INH, our primary endpoint focuses on a decrease in ICP. ICP has been used as a surrogate endpoint for inflammation and testing of neuroprotective agents in many prematurely halted or failed clinical trials [37]. This might be due to the fact that ICP is an early surrogate marker during TBI but confounded by the modern neuro-ICU practices through escalating interventions (such as decompressive craniectomies (DC)) to immediately mitigate surges in ICP resulting in reduction of its sensitivity, as representing “severity of disease.” Therefore, this trial will focus on the intensity of ICP-targeted therapy based on the Therapy Intensity Level (TIL) Scale [38, 39]. The TIL Scale is designed to integrate all known and relevant ICP directed treatments into a single-summary score and was developed as part of the Interagency Common Data Elements scheme [38]. Since its introduction, the novel TIL Scale has been widely used in neurotrauma research, with excellent inter- and intra-rater reliability with minimal measurement errors [39]. The TIL Scale includes eight ICP treatment modalities each with a certain numerical score. Added together, TIL ranges between 0 and 38 points with a right-skewed distribution. Specifically, TBI patients admitted to the ICU have an average TIL score of 8.2 (SD 3.2), while general trauma patients on the ICU have a score of 2.2 (SD 0.9) [39]. The daily score will be calculated based on the highest score in each item per day (TIL24), to provide a metric on the maximal therapeutic intensity for ICP management for that day. The TIL score will be based on the highest TIL24 during the days an ICP monitor is in place (TILmax) and will be scored by a trained research team, and according to an SOP, thereby optimizing inter- and interrater reliability.

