
### Sample size

To detect a between-group difference in the TIL Scale of 2.2, with 90% power and 0.05 (two-sided) significance level, a total of 106 patients are required. Calculations were based on the anticipated mean of 8.2 and standard deviation 3.2 of the novel TIL in TBI patients admitted to the ICU [38]. The patient group treated with C1-INH is estimated to have an average TIL of 6 [39, 51]. Both treatment groups will include 53 patients to power the trial and to account for withdrawal and loss to follow-up (approximately 10%). With this sample size, a difference of 2.2 on the TIL scale can be detected, which is clinically relevant as it corresponds to one medium level of intervention (such as CSF drainage or mannitol treatment) less to control ICP indicating a significant treatment effect. As no minimal clinically important difference (MCID) for the TIL scale is defined in the literature, we will adhere to this shift of 2.2 points on the right-skewed scale.

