### Statistical analysis

The trial profile will be summarized using a Consolidated Standards of Reporting Trials (CONSORT) flow diagram, including the reasons for non-eligibility and non-enrollment [52]. The data will be analyzed on an intention-to-treat basis with all randomized patients included in the analysis. Baseline variables will be summarized using descriptive statistics. In line with the IMPACT recommendations, the investigators plan to analyze the primary outcome TIL by using a linear model with covariate adjustment for age, GCS, and pupillary reactivity to adjust for baseline imbalances and to optimize statistical efficiency [53]. TIL will be analyzed as the TILmax for each patient, and the median for each group will be calculated. The treatment effect estimated will be based on the adjusted mean differences including 95% confidence intervals. To maintain the 5% familywise error rate, while still comparing the multiple clinically relevant endpoints, we will use a serial gatekeeping approach for statistical testing [54]. Analysis of GOSE at 6 months, as an ordinal outcome, will be done only if a significant difference in TIL is found. The co-primary endpoint GOSE will not primarily be used to declare the study success. For the analysis of GOSE at 6 months, covariate adjustment for the strongest predictors of outcome in TBI will be performed as mentioned above. The effect estimate will be an adjusted proportional odds ratio with 95% confidence interval for the shift in the direction of a better outcome on the GOSE. The ordinal regression model assumes that the odds ratio for each potential cut of the GOSE is constant no matter which cutoff point is taken (proportional odds assumption). Although the common odds ratio is formally only valid if the proportional odds assumption is met, the common odds ratio can be interpreted as a summary measure of treatment effect, even if the odds ratios differ by cutoff [55, 56]. In this study, the resulting single, common odds ratio can be interpreted as the average shift over the GOSE scale at 6 months caused by C1-INH compared to placebo [56].

Secondary analyses will be compared between the treatment groups using unadjusted and adjusted (ordinal) logistic and linear regression. Time-to-event analyses will be undertaken using Kaplan-Meier curves, as well as Cox proportional hazards regression models.

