### Ethics

The study protocol was designed in accordance with the ethical principles in the Declaration of Helsinki and the regional regulations, and the principles of Good Clinical Practice. Participants will be assessed for eligibility by the neurosurgical resident or research physician when an ICP monitor is placed within 12 h from trauma. Within this time frame, informed consent must also be obtained. Ideally, the treating physician will obtain informed consent from the patient. As the enrolled subjects will lack capacity to consent due to their level of consciousness at presentation, informed consent can be obtained within 12 h after trauma by a legally authorized representative of the patient. As TBI mostly occurs outside the domestic situation, family members are rarely available during the first hours after trauma [57]. Therefore, the treating physician will take responsibility for including the patient using “deferred proxy consent” if the following condition are met and documented: (1) the patients is in a potentially life-threatening situation and (2) the patient meets the eligibility criteria for trial entry. As there is a potential benefit with the administration of C1-INH and an urgent therapeutic timeframe of 12 h, deferred consent is justified in these patients [58–60]. Following enrollment via deferred consent, informed consent should still be obtained by a legal representative within 7 days after admission. Furthermore, the patient must agree to further participate in the study when mental capacity is regained. When consent for study continuation is provided, already collected data can be used. When study continuation is refused, already collected data can still be used when patients and/or proxies do not use their right to refuse this. Patients or proxies should always be informed about their right to refuse the use of obtained data. A team of dedicated research nurses and physicians are trained to perform the specific informed consent and randomization procedures. Moreover, a 24/7 study consultation telephone number can be reached to help with problems or questions during the study.

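### The ICP device in place at randomisation can predict TILmax through CSF drainage, but it is not among the covariates of the primary TIL model: a modest, avoidable loss of precision

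*Protocol article*

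**What the plan says.** Either monitor type qualifies a patient. The eligibility section asks for "invasive intracranial pressure monitoring by intra-parenchymatous transducer or ventricular catheter placement", and the ethics section has eligibility assessed "when an ICP monitor is placed within 12 h from trauma". The device is therefore in place before randomisation.

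On the endpoint, the TIL section states: "The TIL Scale includes eight ICP treatment modalities each with a certain numerical score". It does not list the items or their points. The score analysed, TILmax, is the highest daily score over the days with a monitor in place. The sample size section justifies the 2.2-point target because it "corresponds to one medium level of intervention (such as CSF drainage or mannitol treatment) less to control ICP". The trial interventions section takes CSF samples, including one before dosing, where an external ventricular drain "is placed as part of standard care to reduce CSF pressure", and leaves other care to local protocols.

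The statistical analysis section specifies a "linear model with covariate adjustment for age, GCS, and pupillary reactivity" for TIL, to deal with baseline imbalance and to gain efficiency. Randomisation is stratified by centre only. The device is not a stratification factor, a covariate or a subgroup.

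**The concern.** TIL records treatment given, so equipment already in place can matter for it in a way that it may not for GOSE. A patient with a ventricular catheter can have CSF drained at once. A patient with only a parenchymal transducer would first need a drain. If device groups differ in TILmax for this reason, device is a baseline predictor of the primary outcome.

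The article fixes a covariate list for this model and gives it exactly the purpose that such a predictor would serve. The list follows the IMPACT recommendations and is reused for GOSE, and it leaves out a variable linked to an item of TIL. What is at stake is the precision of the TIL comparison and its protection against a chance excess of catheters in one arm. GOSE is tested only if TIL is significant, so a borderline TIL result would also decide whether GOSE is tested.

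**Working it through.** **Inputs from the article.** Target difference 2.2; SD 3.2 (variance 3.2² = 10.24); power 90%; two-sided 0.05; 53 per arm, allowing about 10% loss, so 53 × 0.9 ≈ 48 evaluable per arm.

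**Assumptions.** The article does not give the catheter share p or the net TILmax difference s between device groups. I take p = 0.2 to 0.5, with s = 1 and s = 2.2. The value 2.2 is an upper scenario: it supposes that every catheter patient gains the full value of a medium-level intervention and that no transducer patient makes it up by other means.

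**The plan's own figure.** The normal approximation gives n = 2 × (1.960 + 1.282)² × 10.24 / 2.2² = 44.5, so 45 per arm. A two-sample t-test needs 46 per arm; 46 / 0.9 = 51.1, so 52 per arm or 104 in total. The stated 106 is reproduced to within 2 patients.

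**Variance explained by device** = p(1 − p)s² / 10.24:

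| s | p = 0.2 | p = 0.5 |
|---|---|---|
| 1 | 0.16 / 10.24 = 1.6% | 0.25 / 10.24 = 2.4% |
| 2.2 | 0.774 / 10.24 = 7.6% | 1.21 / 10.24 = 11.8% |

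**Gain from adjustment**, if SD 3.2 already includes the device mix. The adjusted SD is √(10.24 − p(1 − p)s²). Power at 48 per arm is Φ(2.2 / (SD × √(2/48)) − 1.96).

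| Case | SD | Power at 48 per arm |
|---|---|---|
| Unadjusted | 3.20 | 92.0% |
| s = 1, p = 0.2 | 3.18 | 92.4% |
| s = 1, p = 0.5 | 3.16 | 92.6% |
| s = 2.2, p = 0.2 | 3.08 | 93.9% |
| s = 2.2, p = 0.5 | 3.00 | 94.8% |

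**If the device variance instead comes on top of SD 3.2** and is left unadjusted, with s = 2.2, the SD is 3.32 to 3.38 and power at 48 per arm is 90.1% to 89.0%.

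**Chance imbalance.** The SD of the shift in the treatment estimate is s√(2p(1 − p)/53):

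- s = 2.2: 0.17 to 0.21 points, a 95% range of about ±0.34 to ±0.42.
- s = 1: 0.08 to 0.10 points.
- The planned standard error is 3.2 × √(2/53) = 0.62. If 3.2 covers the device mix, the chance shift is already inside it. Adjustment at s = 2.2 would bring the standard error to 3.08 × √(2/53) = 0.60 or 3.00 × √(2/53) = 0.58.

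**The case against.** The strongest reply is that the device scores nothing; treatment does. A catheter earns drainage points only if CSF is drained. The sample size section puts mannitol beside drainage as a medium-level intervention, so a transducer patient who needs ICP control may collect similar points another way or receive a drain later. The net device difference could be well below 2.2, even near zero. This stands, and it is why 2.2 is only an upper scenario.

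A reader might infer that device choice biases the trial, because two patients may differ by the whole target effect. The documents do not support that. Allocation is randomised and blinded and the device precedes it, so the expected bias is zero. A difference between two patients is not a difference between arms. Stratification by centre may also limit imbalance if device choice follows local practice.

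It can also be said that a set based on the IMPACT recommendations is defensible, that omitting one prognostic variable is no error in a randomised trial, and that the unseen analysis plan may add it. The first two hold, which limits the point to an improvement. As to the third, the article does fix the covariates for this model, so the list can be judged as it stands.

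**Conclusion.** The point holds as a gain in efficiency. The device at randomisation can predict TILmax, it precedes allocation, and the stated model leaves it out. The cost is lost precision and less protection against chance imbalance. With 20-50% catheters assumed, adjustment adds under 1 percentage point of power if devices differ by 1 point, and about 2 to 3 percentage points if they differ by 2.2. The gain would be smaller if device choice is already partly explained by the three planned covariates.

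A reader might go further and conclude that the sample size fails. It does not: 106 is reproduced closely, and even with device variance added on top at s = 2.2, power stays at about 89% or more.

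**What to change.** In the statistical analysis section, add the ICP device in place at randomisation (ventricular catheter versus parenchymal transducer only) to the covariates of the TIL model. State that drains placed after randomisation are not adjusted for, because they are part of the outcome. An analysis of TILmax without the CSF-drainage item is not needed: it would change the scale and discard part of what the treatment might affect.

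The cost is one sentence and one degree of freedom. Entry depends on the monitor, so its type is known for every patient. The change touches no clinical care and should be made before unblinding, so that it cannot look data-driven.
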